### Power analysis

An a-priori power analysis has been conducted using G*Power (version 3.1.9.6). We expect to find small, but relevant effects and therefore used an effect size of *f* = 0.14 for power calculation (*f*^2^ = 0.02). We intend to achieve a power of 1 – β = 0.95 and used a Bonferroni-adjusted α-level of α_adjusted_ = 0.05/3 = 0.017 (see data preparation and statistical analysis). With these parameters a total sample size of *N* = 174 (29 per condition) is needed for an analysis of variance for repeated measurements (rmANOVA) with six measurement time points and six conditions. Based on our experience with similar studies, we expect a small drop-out rate of about 10% due to insufficient saliva or blood volumes and will, therefore, recruit additional 18 participants (3 per condition). This results in a total sample size of *N* = 192.

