### Biological and physiological outcome measures

Main outcomes will be measures for physiological stress responses, which will be assessed via saliva and capillary blood samples as well as by means of electrocardiogram (ECG) recordings. An overview is provided in Table 2. As measures for SNS re-activity, salivary alpha-amylase [67] as well as the participants’ heart rate will be used. PNS re-activity will be assessed from heart rate variability (HRV) measures [e.g., root mean square of successive differences of consecutive R-R intervals (RMSSD); 68]. Activity of the HPA axis will be assessed via salivary cortisol measurements, which will be collected by means of *Salivettes* (Sarstedt, Nümbrecht, Germany). IL-6 and CRP will be assessed from capillary blood samples, which will be measured in Dried Blood Spots [69,70], which is an established procedure in our group [e.g., 71,72]. s-IgA will be measured in unstimulated saliva samples, which will be collected by means of *Salicaps* (IBL international, Hamburg, Germany).

**Table 2 pone.0263785.t002:** Biological and physiological outcome measures, number of samples, collection time point, and assessment procedure.

Stress system	Outcome measure	Number of time points	Time points	Procedure
Sympathetic Nervous System	Salivary-alpha amylase	6	Baseline, +0, +10, +20, +45, +90 minutes	Stimulated saliva samples
	Heart rate	NA	Continuously (baseline to + 90 minutes)	Electrocardiogram
Parasympathetic Nervous System	Heart rate variability (RMSSD)	NA	Continuously (baseline to + 90 minutes)	Electrocardiogram
HPA axis	Cortisol	6	Baseline, +0, +10, +20, +45, +90 minutes	Stimulated saliva samples
Immune system	CRP	3	Baseline, + 90 minutes, +24 hours	Dried Blood Spots
	IL-6	3	Baseline, + 90 minutes, +24 hours	Dried Blood Spots
	s-IgA	2	Baseline, +90 minutes	Unstimulated saliva samples

*Note*. CRP: C-reactive protein; HPA: hypothalamic-pituitary adrenal; IL-6: interleukin-6; s-IgA: secretory immunoglobulin-A; NA: not applicable; RMSSD: root mean square of successive differences.

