### Data preparation and statistical analysis

For statistical analysis, IBM SPSS Statistics (version 26 or higher for Windows) will be used. Data will be screened for outliers, and outliers which differ more than 3 standard deviations from the participants’ mean will be excluded from further analysis. Test of normality will be conducted by means of the Kolmogorov-Smirnov test. If necessary, data will be transformed (e.g., by means of the natural logarithm or square root transformation) to achieve a normality distribution.

For main hypotheses testing (research questions 1, 2, and 3), rmANOVAs will be conducted. In the analyses, the between-subjects factor ‘Condition’ (with six levels, see above) as well as the within-subjects factor ‘Time’ (with either six levels (for sAA, cortisol, and ECG measures), two for CRP and IL-6, and two for s-IgA) will be included. Three separate analyses will be conducted, one for SNS and PNS markers (i.e., sAA, HR, and RMSSD) and six measurement time points (s_1_ to s_6_), one for cortisol as the only HPA-axis marker with the same six time points, and one for the immune parameters (i.e., IL-6, CRP, and s-IgA) and two measurement time points. An additional factor ‘Measure’ (e.g., with the levels IL-6, CRP, and s-IgA for immune parameters) will be included if necessary. A Bonferroni-adjusted α-level of α_adjusted_ = 0.05/3 = 0.017 will be used for the main analyses, because three separate rmANOVAs will be conducted. The potential confounders age, sex, BMI, use of oral contraceptives and menstrual cycle phase for female participants, as well as time of day will be included in all statistical analyses as covariates.

Research question 4 (i.e., perceived stress, state anxiety, and affect) will be investigated analogously to research questions 1 to 3 by means of a further rmANOVA. The same α_adjusted_ = 0.017 as for main hypothesis testing will be used. For analysis of research question 5 (i.e., associations with person characteristics and psychological variables), nominal scaled variables (e.g., sex and education) will be included as additional factors in further rmANOVAs. For metric variables, multivariate regression analyses will be conducted in which the potential moderator variables will be included as moderator variables. For these analyses, the SPSS macro PROCESS [102] will be used. For these analyses which refer to research question 5, an adjusted α-level of α_adjusted_ = 0.001 will be used.

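### Baseline is analysed as a level of Time rather than as a covariate: the test is valid, but it gives up power, mainly in the two-time-point immune analysis

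*Protocol article*

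**What the plan says.** Under Data preparation and statistical analysis, the within-subjects factor Time is defined "with either six levels (for sAA, cortisol, and ECG measures), two for CRP and IL-6, and two for s-IgA". The autonomic analysis uses s_1 to s_6, and the cortisol analysis is "one for cortisol as the only HPA-axis marker with the same six time points". Table 2 gives these times as "Baseline, +0, +10, +20, +45, +90 minutes". Experimental setting and procedure places s_1, DBS_1 and us_1 at the end of the rest period, before the main task is introduced. s-IgA is sampled only at baseline and +90 minutes, so its two levels must include baseline.

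The covariates for all analyses are age, sex, BMI, oral contraceptive use, cycle phase and time of day. The baseline value of the outcome is not among them.

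The sample size comes from the Power analysis section: "used an effect size of *f* = 0.14 for power calculation", "used a Bonferroni-adjusted α-level of α_adjusted_ = 0.05/3 = 0.017", "We intend to achieve a power of 1 – β = 0.95", for an "rmANOVA) with six measurement time points and six conditions", with the result that "a total sample size of *N* = 174 (29 per condition) is needed". The section gives no correlation between time points and no power for a two-time-point analysis.

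**The concern.** The condition has not been delivered when the baseline samples are taken, so randomised groups can differ there only by chance. Baseline therefore carries no information about the effect of condition except through its correlation with later values. Entering it as a covariate uses that correlation with the weight the data support. Entering it as an outcome level in a Condition x Time test with two times fixes the weight at one, because the interaction is then exactly an ANOVA of change from baseline. Whenever r is below 1 this has the larger variance.

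The immune markers are primary outcomes and have one of only three main analyses. That analysis has two time points, while the sample size was computed for six. It is where lost efficiency is most likely to change what the trial can show.

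**Working it through.** **Inputs.** From Power analysis: f = 0.14, alpha = 0.05/3, target power 0.95, k = 6 conditions, m = 6 times, N = 174. From Data preparation and statistical analysis: m = 2 for the immune markers. The correlation r is not stated, so it is varied. Sphericity is assumed and a single marker is modelled.

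**1. Reproduce the plan's N.** For the within-between interaction, λ = f²·N·m/(1-r), with df1 = (k-1)(m-1) and df2 = (N-k)(m-1). With r = 0.5 and m = 6:
- λ = 0.0196 × 174 × 6 / 0.5 = 40.92, with df 25 and 840, giving power 95.4%.
- The smallest N reaching 95% is 172, or 174 in equal groups. The stated N is reproduced, with r = 0.5 as the implied correlation.

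**2. Variance with two time points** (common variance σ²).
- Change score: 2(1-r)σ².
- Baseline-adjusted (ANCOVA): (1-r²)σ².
- Ratio of adjusted to change: (1+r)/2, which is 0.65, 0.75, 0.85 and 0.90 at r = 0.3, 0.5, 0.7 and 0.8.

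**3. Power with two time points.** If condition g shifts the post-task mean by d_g, the interaction terms are ±d_g/2 (d_g centred), so f² = Var(d)/(4σ²) and Var(d) = 4f²σ². Hence:
- As planned: λ = N·4f²/[2(1-r)] = 2Nf²/(1-r), with df 5 and 168.
- Adjusted: λ = 4Nf²/(1-r²), with df 5 and 167.
- At r = 0.5 and N = 174: planned λ = 2 × 174 × 0.0196 / 0.5 = 13.64; adjusted λ = 4 × 174 × 0.0196 / 0.75 = 18.19.

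| r | Planned power, N = 174 | Adjusted power, N = 174 | N for 95%, planned | N for 95%, adjusted |
|---|---|---|---|---|
| 0.3 | 48% | 73% | 435 | 285 |
| 0.5 | 67% | 83% | 313 | 237 |
| 0.7 | 92% | 96% | 191 | 163 |
| 0.8 | 99.3% | 99.7% | 130 | 118 |

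At N = 192 and r = 0.5 the figures are 73% and 88%.

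**4. Six time points.** Under compound symmetry with r = 0.5 and N = 174, the planned Condition x Time test was compared with a joint test on the five post-task values given baseline, holding the interaction f at 0.14. Planned power is 95.4%. Adjusted power is 96.1% if the response is confined to the first post-task sample, and 98.4% to 98.5% if it decays over the session or peaks at +20 minutes. The gain is about 1 to 3 percentage points.

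**The case against.** The strongest reply is that nothing here is an error. A randomised Condition x Time test that includes baseline is valid, and it addresses the stated aim of comparing reactivity over time. This stands. A reader might infer that the planned analysis is biased or asks the wrong question; the article does not support that. The issue is efficiency only.

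Further points that stand:
- The immune shortfall comes first from sizing the trial on six time points and analysing two. Adjustment narrows the gap but does not close it at r = 0.5.
- The figures depend on an unstated r, and at 0.8 the gain is negligible.
- Table 2 lists three times for IL-6 and CRP, against two in the analysis section. With three, planned power at N = 174 by the formula in step 1 is 78% at r = 0.5 and 97.5% at r = 0.7. The optional factor Measure and the planned covariates would also change absolute power.
- It would be too strong to say that precision suffers most in the immune analysis under every response shape. For a response sustained over all five post-task samples, the six-time analyses retain relative information of 0.58 against 0.75 for the two-time case at r = 0.5. The immune analysis has most at stake in power, because the six-time power is already about 95% at that r.
- Baseline as a level is not idle: it is the reference that lets Condition x Time detect a sustained elevation. A test of Condition x Time on post-task values alone would miss one.

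A reader might also infer that repeated-measures ANOVA will discard many participants with a missing sample. The article states no missing-data rule and already allows about 10% for insufficient saliva or blood, so this is not used as an argument here.

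What does not stand is that the matter is merely left to a fuller plan. The article fixes both the levels of Time and the covariates.

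**Conclusion.** The point holds as a loss of efficiency from a stated analysis choice. For a single immune marker with two time points at N = 174, baseline adjustment raises power by about 25 percentage points at r = 0.3, 16 at r = 0.5, 4 at r = 0.7 and less than 1 at r = 0.8. At r = 0.5, the value implied by the article's own N, power moves from 67% to 83%, still below the intended 95%. For transient responses in the six-time-point analyses the gain is minor.

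These figures assume equal variances, sphericity, f = 0.14 carried over from the six-time calculation, one marker at a time, and no contribution from the other covariates. The change is worth making because the baseline samples are collected anyway.

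**What to change.** Analyse post-task values with the outcome's own baseline as a covariate:
- s-IgA: ANCOVA of the +90-minute value on baseline.
- Outcomes with several post-task times: a mixed model with Condition, Time, Condition x Time, baseline and baseline x Time, plus the covariates already listed.
- Primary test: the joint test of Condition and Condition x Time, or prespecified condition contrasts at the hypothesised peak time of each marker, so that a sustained elevation is not missed.

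Equivalently, keep baseline in the outcome vector of a mixed model and constrain its mean to be equal across conditions. This also retains estimates of change from baseline within each condition, which the hypothesis of no HPA response in conditions 3 and 4 needs.

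State the number of time points for IL-6 and CRP consistently with Table 2, and restate power for the immune analysis with an explicit correlation and a range around it.

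The cost is a change of analysis wording and a short power calculation. No extra samples or participants are needed for the adjustment itself, the named software fits these models, and analysis begins only after data collection is complete. If 95% power for the immune markers is still required at r near 0.5, that is a separate sample-size decision.

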### Hypotheses

#### Main hypotheses

With regard to the specificity hypothesis [45,46], we expect that pure digital stressors will trigger physiological responses of the SNS (i.e., an up-regulation), PNS (i.e., a down-regulation), as well as an activation of the immune system, but not of the HPA axis (due to the absence of a social-evaluative component). An additional activation of the HPA axis (i.e., an increase of cortisol levels) is expected for the conditions 5 and 6 (non-digital parallel dual-tasking and multitasking), in which we included a social-evaluative component by the presence of an experimenter.

Our main hypotheses, that are associated with research questions 1, 2, and 3 are:

Conditions 3 and 4 (digital work interruptions and digital parallel dual-tasking) will trigger responses of the SNS, PNS, and the immune system that are stronger than in the passive control condition 1 and the single-task control condition 2. No HPA axis response are expected for conditions 3 and 4.Conditions 5 and 6 (non-digital parallel dual-tasking and multitasking) will trigger responses of the SNS, PNS, HPA axis, and the immune system that are stronger than in the passive control condition 1 and the single-task control condition 2.

Regarding the time course of the physiological responses (if any will be found), we hypothesize fast responses of the SNS and PNS with a maximum immediately after the tasks. The HPA axis response is expected to be delayed with a maximum 20 minutes after the tasks. Slower responses are expected for the immune system with a maximum of 90 minutes after the task for IL-6 and s-IgA and 24 hours after the experimental session for CRP.

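### The immune analysis is fixed at two time points although CRP and IL-6 are sampled at three and CRP is expected to peak at 24 hours

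*Protocol article*

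**What the plan says.** All from the protocol article:

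- **Primary outcomes** include CRP, IL-6 and s-IgA.
- **Biological and physiological outcome measures, Table 2** gives the schedule "Baseline, + 90 minutes, +24 hours" for both CRP and IL-6. For s-IgA the entry is "s-IgA 2 Baseline, +90 minutes".
- **Abstract** and **Experimental setting and procedure** confirm the third blood spot. It is self-collected at home 24 hours after the first and posted back.
- **Main hypotheses** expect a "maximum of 90 minutes after the task for IL-6 and s-IgA and 24 hours after the experimental session for CRP".
- **Data preparation and statistical analysis** sets the levels of the Time factor at "two for CRP and IL-6, and two for s-IgA". The next sentence says the same of the single immune analysis: "one for the immune parameters (i.e., IL-6, CRP, and s-IgA) and two measurement time points". A factor for the measure is added only if needed. Alpha is 0.05/3 = 0.017 because there are three ANOVAs.

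The article describes no other analysis of the 24-hour sample.

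**The concern.** The number of Time levels is a stated rule, not a detail left open, and it conflicts with the article's own schedule and time-course hypothesis. If CRP is compared only between baseline and +90 minutes, it is tested before the time at which the plan expects its maximum. A null result there could be read as absence of a CRP response when the plan's own theory places that response later. If the 24-hour comparison were added once the data are in, it would be a post hoc choice on a primary outcome.

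**Working it through.** **1. Samples against analysed levels**

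| Marker | Baseline | +90 min | +24 h | Time levels in the analysis | Expected maximum |
|---|---|---|---|---|---|
| CRP | yes | yes | yes | 2 | +24 h |
| IL-6 | yes | yes | yes | 2 | +90 min |
| s-IgA | yes | yes | no | 2 | +90 min |

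For CRP and IL-6, 3 − 2 = 1 scheduled time is left out. With one such sample per participant, that is up to 192 blood spots.

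**2. Which time is left out**

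The article does not say, so each possible pair is tried:

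- *Baseline and +90 minutes.* Available for all three markers. It serves the IL-6 and s-IgA expectations. The 24-hour CRP value is unused.
- *Baseline and +24 hours.* Not available for s-IgA. A CRP rise at 24 hours could be tested, but not that it exceeds the +90-minute value. The IL-6 value at its expected peak is lost.
- *+90 minutes and +24 hours.* Not available for s-IgA, and there is no baseline.

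Only the first pair fits one analysis of all three markers. No pair serves the time-course expectations for both CRP and IL-6.

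**3. Is changing the number enough?**

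No. A repeated-measures ANOVA crossing measure with three times needs every measure at every time, and s-IgA has no 24-hour value. s-IgA has to leave the joint model.

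**4. The plan's sample size, and whether power bears on the point**

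Inputs from Power analysis: f = 0.14, k = 6 conditions, m = 6 times, α = 0.05/3, power 0.95. The correlation between repeated measures (r) and the sphericity correction are not given; sphericity is assumed. For the Condition × Time interaction:

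λ = f²·N·m/(1 − r), df₁ = (k − 1)(m − 1), df₂ = (N − k)(m − 1)

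With assumed r = 0.5 and N = 174, λ = 0.0196 × 174 × 6/0.5 = 40.9, df = 25 and 840, and power = 0.954. This reproduces N = 174, and 174 + 18 = 192. Assumed r = 0.3 would need 240 and r = 0.7 would need 108. The figure was computed for six times and is unaffected by this point.

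The same formula at N = 174 and α = 0.05/3:

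| Assumed r | m = 2 | m = 3 |
|---|---|---|
| 0.3 | 0.475 | 0.572 |
| 0.5 | 0.674 | 0.784 |
| 0.7 | 0.924 | 0.975 |

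The levels depend on an unstated r, and the comparison assumes that f stays at 0.14 when a time is added. These figures are not evidence for the point, which rests on steps 1 to 3.

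**5. Alpha after a split**

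Two immune models make four main analyses: 0.05/4 = 0.0125. Three make five: 0.05/5 = 0.01. Applied to all analyses, at r = 0.5 these take the six-time power from 0.954 to 0.943 or 0.934, below the stated 0.95.

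**The case against.** The strongest reply is that this is a slip. Listing CRP and IL-6 apart from s-IgA would be pointless if the counts were equal, so three was probably meant. The abstract, Table 2 and the hypotheses all treat 24 hours as a real assessment. That is plausible, and a reader might wrongly infer that the sponsor chose to discard the sample; the documents do not show that. But the next sentence repeats two, and step 3 shows that correcting the number alone leaves a joint model that cannot be fitted.

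A second reply is that the measure factor is optional, so the joint model is not firm. This stands in part: dropping +24 hours is a strong inference, not stated text. However, separate models per marker would contradict the count of three ANOVAs on which alpha rests.

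A third reply concerns the stakes. A reader might infer that the main hypotheses cannot be answered. The text does not support this. The two numbered hypotheses speak of the immune system as a whole, compared with the control conditions, and do not name CRP. The 24-hour expectation is a separate statement, conditional on responses being found. IL-6 and s-IgA can be tested at +90 minutes as planned, and a +90-minute CRP comparison also remains possible. This objection stands and limits the consequence to CRP's later course.

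Finally, a reader might cite the higher power with three times as a reason for the change. It rests on a correlation that the article does not give, and it is set aside.

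**Conclusion.** Wrong as written. The two-level Time factor for CRP and IL-6 contradicts the three scheduled samples and the expected CRP maximum at 24 hours, and no choice of two times resolves this for both markers. The article does not name the two times. Given the s-IgA schedule and the single immune analysis, the 24-hour values most likely enter no main test.

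What is lost is the ability to show a late CRP response or a CRP maximum at 24 hours, for one of seven primary measures. The condition-level immune hypotheses survive through IL-6 and s-IgA at +90 minutes. The conclusion needs no power assumption.

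**What to change.** 1. In Data preparation and statistical analysis, change the Time levels for CRP and IL-6 from two to three: baseline, +90 minutes and +24 hours. Correct the sentence on the immune analysis to match.
2. Analyse s-IgA in a separate model with its two times.
3. Pre-specify the key contrast per marker: baseline to +24 hours for CRP, baseline to +90 minutes for IL-6 and s-IgA.
4. State how alpha is handled. One option is to divide the immune family's share among its models: 0.0167/2 = 0.0083 for two models or 0.0167/3 = 0.0056 for three. The autonomic and cortisol analyses then keep 0.05/3, which avoids the loss shown in step 5 of the working.

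**Cost.** The samples are already scheduled, so nothing is added to data collection. It is more than a change of wording, because each immune model faces a stricter alpha. As an illustration with the formula above (N = 174, f = 0.14, α = 0.0083), a three-time model has power 0.475, 0.707 or 0.957 at assumed r = 0.3, 0.5 or 0.7. The two-time s-IgA model has 0.379, 0.581 or 0.883, against 0.475, 0.674 or 0.924 at 0.0167.

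### The three main rmANOVAs are each held to a fixed Bonferroni level; this is valid, but Holm's procedure keeps the same 5% familywise error with more power, chiefly for the immune analysis

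*Protocol article*

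**What the plan says.** The section on data preparation and statistical analysis defines three confirmatory analyses:

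- Autonomic markers: "Three separate analyses will be conducted, one for SNS and PNS markers (i.e., sAA, HR, and RMSSD) and six measurement time points".
- Cortisol: "one for cortisol as the only HPA-axis marker with the same six time points".
- Immune markers: "one for the immune parameters (i.e., IL-6, CRP, and s-IgA) and two measurement time points".

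Each is judged at one fixed level, 0.05/3, printed as 0.017, which "will be used for the main analyses, because three separate rmANOVAs will be conducted". No step-down or other sequential rule is mentioned. Research question 4 borrows its level by referring back to the main tests.

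The Power analysis section uses the same level ("We intend to achieve a power of 1 – β = 0.95 and used a Bonferroni-adjusted α-level") with a small effect ("We expect to find small, but relevant effects and therefore used an effect size of *f* = 0.14 for power calculation"). It arrives at N = 174 evaluable participants for six conditions and six time points. No calculation is given for two time points.

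Under Main hypotheses, the second hypothesis says that conditions 5 and 6 "will trigger responses of the SNS, PNS, HPA axis, and the immune system that are stronger than in the passive control condition 1" and in the single-task control. The authors thus expect several systems to respond in the same study.

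**The concern.** A fixed level of 0.05/3 treats each of the three p-values as if nothing were known about the other two. Once one null hypothesis has been rejected, at most two true nulls can remain, and the remaining tests can use 0.05/2. After a second rejection the last test can use 0.05. Holm's procedure does this without any assumption about how the tests are correlated, which suits stress systems measured in the same people.

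The loss is greatest when several systems respond together, which is what the main hypotheses predict. It falls on the weakest test. The immune analysis has two time points where the sample size was computed for six, and it stays at 0.05/3 even when the other two analyses have already been rejected. What is at stake is an avoidable false negative for the immune system, not control of the error rate.

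**Working it through.** **Inputs from the Protocol article.** f = 0.14, so f² = 0.0196; k = 6 conditions; N = 174; per-test level 0.05/3; m = 6 time points for the autonomic and cortisol analyses and m = 2 for the immune analysis.

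**Assumptions not in the document.** Correlation between repeated measures r = 0.5; sphericity; one Condition × Time F-test per system without the optional Measure factor and without covariates; f = 0.14 in all three systems; independent tests.

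**Step 1: reproduce the stated sample size.** For the interaction, λ = N·f²·m/(1 − r), df1 = (k − 1)(m − 1) and df2 = (N − k)(m − 1).

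- m = 6: λ = 174 × 0.0196 × 6/0.5 = 40.92, df 25 and 840. Power at 0.05/3 is 0.954.
- N = 168 gives 0.944, so 174 is the smallest multiple of six that reaches 0.95. The stated N is reproduced, which supports r = 0.5 and sphericity as the settings used.

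**Step 2: power at the three Holm thresholds.**

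| Analysis | λ | df | 0.05/3 | 0.05/2 | 0.05 |
|---|---|---|---|---|---|
| Six time points (each of two) | 40.92 | 25, 840 | 0.9541 | 0.9669 | 0.9829 |
| Immune, two time points | 13.64 | 5, 168 | 0.6736 | 0.7269 | 0.8130 |

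**Step 3: power of each test.** Each p-value falls in one of four bands cut at 0.05/3, 0.025 and 0.05. Summing the 4³ = 64 band combinations under Holm gives:

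- Immune: 0.67 under Bonferroni, 0.81 under Holm.
- Each six-time-point analysis: 0.954 under Bonferroni, 0.978 under Holm.

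**Step 4: all three significant** (descriptive only; see the objection).

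- Bonferroni: 0.9541 × 0.9541 × 0.6736 = 0.613.
- Holm needs all p ≤ 0.05, at least two ≤ 0.025 and at least one ≤ 0.05/3. The first condition alone gives 0.9829² × 0.8130 = 0.7854. Cases with fewer than two p-values ≤ 0.025 remove about 0.0029, and cases with none ≤ 0.05/3 remove less than 0.0001. The result is 0.78.

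**Step 5: sensitivity.**

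| Setting | Immune, Bonferroni to Holm | All three, Bonferroni to Holm |
|---|---|---|
| N = 174, r = 0.3 | 0.48 to 0.61 | 0.31 to 0.51 |
| N = 174, r = 0.5 | 0.67 to 0.81 | 0.61 to 0.78 |
| N = 174, r = 0.7 | 0.92 to 0.97 | 0.92 to 0.97 |
| N = 174, r = 0.5, three immune time points | 0.78 to 0.88 | 0.71 to 0.86 |
| N = 192 (no dropout), r = 0.5 | 0.73 to 0.85 | 0.70 to 0.84 |

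The row with three immune time points is shown because Table 2 lists three samples for CRP and IL-6. If the three tests are correlated between 0 and 0.8 (N = 174, r = 0.5), the all-three figures are 0.61 to 0.67 under Bonferroni and 0.78 to 0.81 under Holm.

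**Step 6: familywise error.** With all three nulls true and independent, both procedures give 1 − (1 − 0.05/3)³ = 0.049. With one or two nulls true, simulation gives 0.017 to 0.033 for Bonferroni and 0.042 to 0.049 for Holm. Both stay within 0.05.

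**The case against.** The plan contains no error here. The correction is valid and prespecified, and the sample size was computed at the corrected level, so the design has already paid for Bonferroni in the analyses it was powered for. That stands, and it is why the gain there is only 0.954 to 0.978.

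Four stronger readings are tempting, and the document supports none of them.

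- **That the study fails unless all three analyses are significant.** No section makes this a success rule. The second main hypothesis lists expected responses, and the three analyses are tested separately. If a joint claim were intended, each test could be run at 0.05 without adjustment, and Holm would not be the natural remedy. The rise from 0.61 to 0.78 therefore describes the design and is not its power.
- **That Bonferroni buys nothing.** When some nulls are true, its familywise error is lower than Holm's, and it also bounds the expected number of false rejections at 0.05, which Holm does not. The protocol's stated correction aims only at splitting 0.05 over three tests, so Holm meets the same 5% standard, but the exchange is not free.
- **That the printed 0.017 breaks error control.** Three tests at 0.017 sum to 0.051, but the figure is plainly 0.05/3 shown to three decimals.
- **That Holm repairs the immune analysis.** Its low power comes mainly from having two time points where six were assumed. With six time points in all three analyses, the all-three figures would be 0.87 and 0.95.

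The size of the gain also depends on r and on the number of immune time points, as the sensitivity table shows. Its direction does not.

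**Conclusion.** The point holds as one of efficiency, not of validity. A fixed 0.05/3 controls the familywise error, and Holm controls it at the same 5% and is never less powerful. Under the protocol's own f and N, with r = 0.5, sphericity, independent tests, equal effects and no Measure factor, immune power rises from about 0.67 to 0.81. It stays below the planned 0.95, and the six-time-point analyses gain about 0.02. The immune gain relies on the other two systems responding, since only then does the last threshold open to 0.05. It is small where power is already high (0.92 to 0.97 at r = 0.7). Because the cost is close to nil and the main hypotheses expect several systems to respond, the change is worth making.

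**What to change.** Make three edits, dated and documented before any analysis:

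1. In Data preparation and statistical analysis, replace the fixed level with: *The p-values of the three main rmANOVAs are tested with Holm's step-down procedure at a familywise level of 0.05: the smallest against 0.05/3, the next against 0.05/2, the largest against 0.05, stopping at the first non-rejection.* Use unrounded thresholds.
2. In the same section, give the level for research question 4 explicitly as 0.05/3. Its present reference to the level of the main tests would otherwise point to nothing.
3. In Power analysis, add that N = 174 was computed at the first Holm step. The number itself stands, because power can only rise.

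No further participants, samples or measurements are needed. Data collection has started, so this is a documented change after the start; the protocol plans no interim or preliminary analyses, so it can be fixed before results are seen. The costs are a higher familywise error than Bonferroni's when only some nulls are true (still at most 0.05) and simultaneous confidence intervals that no longer match the tests exactly.
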